#### Length of stay data

Development of data for analysis of patients' length of stay is identical to the process for readmission data. Length of stay will be calculated as the number of days between the dates of the start and end of each admission. If both dates are the same then the length of stay will be 0 days.

#### Collaboration survey data

The purpose of the survey is to measure staff members' perceptions of interprofessional collaboration. It is an adaptation of the Collaboration Among Medical Staff Subscale (CMSS) from the Nurses' Opinion Questionnaire [21] The CMSS measures professional working relationships among nurses, physicians, and other health care professionals. It was developed on a belief that the organizational structure, role behavior, and communication patterns and methods between caregivers affect patient outcomes and staff satisfaction. Validity and reliability of data from published versions of the CMSS have been acceptable [22,23].

We will administer an adaptation of the CMSS containing 28 question items, fourteen unique items presented twice on one page, with vocabulary changed slightly to reflect the two major groups of GIM staff with whom a respondent works. Physicians will respond to survey items that target nurses, allied health staff, and unregulated clerical and clinical support workers; nurses respond to survey items targeting physicians, allied health staff, and unregulated clerical and clinical support workers; and allied health staff respond to survey items targeting physicians, nurses, and unregulated clerical and clinical support workers. The survey will be coded so that higher scores will represent higher perceived importance and existence of interprofessional collaboration within the team.

We plan three administrations of the survey instrument. The first will occur as close as possible to the first day of intervention implementation in the GIM teams. The second administration will occur after full implementation of the study's interventions, about eight weeks later. The third will occur eight weeks after the second.

In randomized trials, data from participants who are unaware of the past group condition, treatment or control, can be valuable [24,25]. Accordingly, the third survey administration will have particularly strong potential to survey staff who joined their GIM division and CTT after the conclusion of the intervention, eight weeks post-intervention. We expect that these staff members will be naïve to the past group condition of the clinical teams with which they are presently working.

In some of the hospital sites nursing and other health professionals' responsibilities require them to work on both intervention and control group teams; in these sites the survey instrument will direct survey respondents of these groups to self-select the team they work with most often from a complete list of the site's four GIM teams participating in the trial.

#### Patient satisfaction data

Patient satisfaction survey data is collected from post-discharge surveys of consenting Ontario hospital patients. Surveying is performed by the NRC+Picker company on behalf of a partnership initiative between the Ontario Hospital Association (OHA) and the Ontario Ministry of Health and Long-Term Care. Most of these data are analyzed and consolidated for reports published on an annual basis by Ontario's Hospital Reports Research Collaborative. The initiative includes a major program to measure acute care inpatients' satisfaction with their hospital stays. These data are typically held in our hospital sites' offices of quality improvement or risk management.

We will identify individual question items and dimensions in the OHA/NRC+Picker reports with potential to be impacted by the effectiveness of interprofessional collaboration among GIM division staff. We will attempt to obtain frequency distributions of patients' individual-level responses to these questions from hospital databases. Some data may be aggregated; individual responses may not be available. In these instances we will attempt to obtain percentages of respondents reporting positive scores on the question items and dimensions. Patient satisfaction data can be sorted and filtered into team-level groupings and can be accessed over the Internet at some of the participating hospitals sites. At other sites we will require assistance from hospital administrative functions to achieve linkages between responses and the teams where patients were treated.

#### Paging activity

For investigations of paging activity, potential subjects are GIM staff members who carry and use a hospital paging device. Development of a paging activity dataset will require assistance from two key resources: (1) GIM administrative functions that can identify GIM team members who carry pagers, and (2) reporting functions in a hospital site's information and communications technology division that can generate analytic reports of pages placed to GIM team members.

Administrative assistants in the hospital sites' Departments of Medicine will provide on-call schedules for medical staff members. On-call medical staff members carry pagers to provide coverage in various positions in the Department of Medicine, including GIM. Patient care managers in GIM teams will identify for us members of their team's nursing and allied health staff who carry paging devices.

After we have obtained the required information to identify individuals and positions in GIM that carry pagers, we will approach information technology reporting functions with the information. When we supply titles of GIM positions that carry pagers and paging identification numbers assigned to them, information technology staff is able to generate reports that can be used to determine the number of pages received by a specific paging identification number, and some other important characteristics of pager calls, chiefly, their designation as urgent or normal.

Recently we undertook exploratory conversations with members of two hospital sites' information technology divisions. Our goal was to probe the general character of paging records (i.e., data fields, content, frequency) that might be available for research use. These conversations suggested two key factors for consideration. First, while the nature of the request and the use of the data or reports in which the data routinely appear would be unusual, it is possible to generate time-delimited reports of activity on a selectively targeted group of paging devices. The second factor we learned is that there is a possibility that calls to paging devices can contain patient health information or other identifying information, and this information could also appear in administrative records of paging activity.

We appreciate the need to grant supreme confidentiality to both patient information and non-patient-related thoughts and expressions that staff members might convey to one another in their paging activity. For these reasons we will limit our requests to include only the minimum essential amount and character of information required to test our hypotheses. In particular, we will request that staff of the sites' information technology departments *remove/exclude *all personal health information and patient identifying information from any records and reports that are provided to us. This would include text that could appear in records relating to paging devices with alphanumeric capability.

We will request that information technology staff members *include *in records or reports: the number of the device receiving the page, the role/function to which it is assigned (e.g., Patient Care Manager, Occupational Therapist, Attending Staff Physician), the date and time the page was received by the device, the urgent/non-urgent status associated with the page and, if possible, the number and role/function which placed the call to the paging device.

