### Intervention

The intervention is a four-step collaborative communication protocol, a quasi-script for face-to-face, collaborative interprofessional interaction. We will ask GIM staff members and trainees to use the four following steps when they have face-to-face patient-related interactions with individuals whom they know (or believe) are members of a different professional group than their own:

1. Name – Introduce oneself to the member(s) of the other profession by name;

2. Role – State to the other interactant(s) one's own professional role in the team or GIM division and describe it with respect to the target patient under discussion;

3. Issue – Share with the member(s) of the other profession one's unique, profession- and training-specific issues, problems, or plans relating to the target patient under discussion; and

4. Feedback – Elicit interaction-specific feedback from the other participant(s) in the interaction by using prompts such as, "Do you have any concerns?" or, "Is there something else I should consider?"

These four steps illustrate our approach to two key intervention goals. First, by continuously introducing oneself by name and role in relation to a specific patient, the typical social barriers in a rapidly changing GIM division – role confusion and anonymity – are reduced. Second, by sharing one's professional perspective and eliciting a collegial point of view, opportunities to solve a patient care problem and/or extend care beyond the limits of uniprofessional practice are elevated.

For GIM medical staff and trainees, intervention implementation will begin in the orientation of a new rotation of medical residents by a team's attending staff physician. This orientation is regularly scheduled during the first week of the rotation. We will enlist the attending physician of each GIM division's two intervention-group medical teams to explain and promote the importance of each of the above mentioned communication behaviours to his or her resident team physicians. Likewise, the same promotional activity will be offered by other professional staff leaders in the intervention CTTs to the professionals who report to them, nurses and allied health professionals. For all professional leaders there will be frequent, opportunistic reinforcements in formal or informal meetings, in one-to-one or group uniprofessional or interprofessional settings.

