Implementation will be augmented in the following ways. First, we will establish a broad network of core "faculty advocates" in the intervention teams. Advocates will act as role models and provide direct verbal instruction to their colleagues on the team. We will ask the Patient Care Managers (or equivalents) on intervention teams to enlist the support of staff members who are willing to champion the intervention. Second, advocates will receive initial training about the intervention etiquette from research staff. Third, researchers will provide consultation to advocates to support them in the training, implementation, and uptake goals. Finally, we will use email as a delivery channel to inform advocates of the latest research results and to offer suggestions for reinforcement throughout the duration of the study. The responsibility for implementation of the intervention therefore is shared by researchers and staff-participants in GIM. We anticipate that these combined initiatives will promote increased buy-in and uptake among front line staff-participants in the GIM experimental teams.

In each intervention CTT we expect that thirty minutes will be required to explain the intervention to professional leaders and to field questions. We expect it will take ten minutes of discussion by each of the professional leaders with their trainee or reporting colleagues in each profession. We expect that the time cost of reinforcement will be fleeting, and might occur two or three times per week, at such times as regular rounds or meetings within professions, in interprofessional team meetings, in individual supervision and education meetings, and in opportunistic conversations.

The intervention will run approximately eight weeks in the intervention CTTs. In this time it will expose two rotations of staff and resident physicians and the other health professional staff with whom they work on the teams to the communication and collaboration script. At each hospital site, staff and patient outcomes related to each of the two intervention and control health care teams will be compared.

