### Randomization

#### Sequence generation

The trial is a cluster randomized trial. Stratification is by hospital site. Each stratum has exactly four GIM clinical teaching teams. In five hospital sites, each of four GIM clinical teaching teams will be randomized to intervention or control group status using numbers generated at random by the web site [28], a website service for generating random numbers. Two clinical teaching teams will be intervention teams; two others will be control teams. Assignment of teams is not performed in 'batch mode.' In other words, each unique hospital site's four teams will be assigned a group status with just a few months' lead time, usually after the conclusion of the intervention period at a previous site.

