#### Paging activity

Recent research has suggested that hospital paging systems can be problematic. Paging activity can be highly interruptive. Calls to staff are often clinically inappropriate or not urgent enough to justify a necessary quick callback [33]. Paging can be disruptive to patient care [34] and scheduled rounds [35,36]. Disruptive pages may cause medical errors [37].

If the intervention is implemented correctly, face-to-face communication could increase in frequency and effectiveness. By implication, we suggest that there is potential for reductions in paging activity within and between members of GIM professions.

Administrative records will permit us to examine the total number of pages placed to paging devices of staff members of intervention and control teams, and the number of pages marked as urgent. Numbers of pages to intervention or control teams will be standardized by the number of individuals who carry pagers in the groups. Intervention-control group differences will be examined with linear mixed models.

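### For nursing and allied staff, managers whose trial role differs by arm name the pagers that set both numerator and denominator of the paging outcome, and the only rule for staff shared between arms is written for the survey

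*Protocol article*

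**What the plan says.** Hypothesis 6 (Protocol article, Objectives: hypotheses) expects fewer pages to staff of intervention teams. The Paging activity section under Outcomes: measurement names two sources for the devices. For physicians: "Administrative assistants in the hospital sites' Departments of Medicine will provide on-call schedules for medical staff members". For the other professions: "Patient care managers in GIM teams will identify for us members of their team's nursing and allied health staff who carry paging devices". The next step is described as follows: "After we have obtained the required information to identify individuals and positions in GIM that carry pagers, we will approach information technology reporting functions". IT then reports on the pager numbers it has been given. The Paging activity section under Statistical methods defines the comparison: "Numbers of pages to intervention or control teams will be standardized by the number of individuals who carry pagers in the groups".

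Other sections bear on who makes that list and what they know:

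- Intervention: the researchers will "ask the Patient Care Managers (or equivalents) on intervention teams to enlist the support of staff members who are willing to champion the intervention".
- Sequence generation: "each unique hospital site's four teams will be assigned a group status with just a few months' lead time".
- Allocation concealment says that assignment cannot be concealed. Blinding names paging among the outcomes that will be hard to mask.
- Collaboration survey data says that at some sites nurses and other professionals serve teams in both arms. In the survey these respondents choose the team they work with most. Covariates describes staffing arrangements under which nurses or allied staff cross teams.

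**The concern.** Page counts come from system records and are about as objective as an outcome gets. The step that is not objective is deciding which devices belong to which team. For nursing and allied staff that step is given to each team's manager. Managers on intervention teams have a task in the trial that control managers do not have, and nothing in the stated procedure keeps the arm from them.

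If the two groups of managers attribute carriers differently, pages per carrier can differ between arms with no difference in paging. The room for judgement is widest for a nurse or therapist who works with an intervention team and a control team at the same site. A result on Hypothesis 6, in either direction, could then partly reflect the list. The Discussion singles out paging frequency as one of two outcomes able to test novel hypotheses, so the comparison should be protected.

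**Working it through.** **What the sections establish together**

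1. *Source.* Patient care managers are the only stated source for nursing and allied carriers. Medical pagers come from departmental on-call schedules and are outside this point.
2. *Numerator.* IT reports on the devices it is given, so the list decides which pages are counted.
3. *Denominator.* Pages are divided by the number of carriers, so the same list decides the divisor.
4. *Role by arm.* Only managers on intervention teams are asked to enlist champions.
5. *Knowledge of arm.* Allocation is open, and masking of paging data is described as difficult.
6. *Judgement.* Carrying a pager is a fact. Belonging to one team is not always a fact where staff cross teams, and the tie-breaking rule covers survey respondents only.
7. *Unit.* The listing step speaks of individuals and positions, while the denominator is individuals. A device passed between shifts could count once or several times.

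**How far a list can move the rate**

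The protocol gives no page volume, number of carriers or power figure for paging, so there is no stated figure to reproduce. Every value here is assumed. Take a team with 8 medical pagers at 15 pages a day and 7 nursing or allied pagers at r pages a day, pooled into one rate. With k nursing or allied pagers listed,

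rate(k) = (8 × 15 + k × r) / (8 + k)

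| r | full list, k = 7 | two omitted, k = 5 | two added, k = 9 |
|---|---|---|---|
| 2 | 134/15 = 8.93 | 130/13 = 10.00 (+11.9%) | 138/17 = 8.12 (−9.1%) |
| 5 | 155/15 = 10.33 | 145/13 = 11.15 (+7.9%) | 165/17 = 9.71 (−6.1%) |
| 10 | 190/15 = 12.67 | 170/13 = 13.08 (+3.2%) | 210/17 = 12.35 (−2.5%) |
| 15 | 225/15 = 15.00 | 195/13 = 15.00 (0%) | 255/17 = 15.00 (0%) |
| 25 | 295/15 = 19.67 | 245/13 = 18.85 (−4.2%) | 345/17 = 20.29 (+3.2%) |

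For shared staff, one team's gain can be another's loss. Take two otherwise identical teams, one per arm, and move two shared carriers from the control list to the intervention list. The intervention-to-control ratio becomes rate(9)/rate(5): 8.12/10.00 = 0.81 at r = 2, and 20.29/18.85 = 1.08 at r = 25. Moving them the other way gives 10.00/8.12 = 1.23 and 18.85/20.29 = 0.93. These are ratios for one pair of teams. The effect on the whole comparison depends on how many sites share staff.

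The shift is nil only when the affected pagers carry the team's average load, and its sign depends on whether they carry less or more than that.

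**The case against.** The case against has several sound parts.

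- The article does not say when the list is made. A condensed report may leave that to the full protocol, and silence on timing is not a fault. A reader might infer that the list is drawn up after allocation, but the text gives only the order of listing and the IT request. This point therefore does not rest on timing. It rests on the stated procedure, in which the list comes from people whose trial role differs by arm under open allocation.
- A reader might infer that the managers are themselves engaged to promote the script. The text says only that they are asked to find willing champions. The statement that "the same promotional activity will be offered by other professional staff leaders in the intervention CTTs to the professionals who report to them" concerns professional leaders and does not name patient care managers.
- A reader might infer that intervention managers would pad the list with rarely paged staff and so lower their rate. Nothing supports this. Staff who really carry pagers belong in the denominator, IT records return device number and role, and nothing says that managers will know the hypothesis or how the rate is formed. The table also shows shifts in both directions, so a single favourable percentage would mislead.
- The Blinding section already admits the difficulty for paging data. That discloses the exposure but does not reduce it.
- A list frozen months ahead may go stale, because staff include temporary and casual employees. This is a fair practical objection. Listing device positions, with updates from IT records, answers most of it.

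What remains is team attribution. Checking that a pager exists does not settle which arm a shared carrier's pages belong to.

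**Conclusion.** The point holds in a limited form. For nursing and allied staff, the stated procedure lets managers with arm-dependent roles fix both parts of the paging rate. Where staff work across arms, no rule for the paging outcome says which team they count towards, so attribution can differ by arm.

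The documents do not allow the direction or size of any bias to be stated. The range of −9.1% to +11.9% for one team's rate rests on assumed page volumes and carrier numbers, on a difference of two listed carriers, and on pooling medical with other pagers. It shows that the rate is sensitive to the list, not that bias will occur. Medical pagers, the counting of pages and the primary readmission analysis are unaffected. This is a minor, inexpensive improvement to a secondary outcome.

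**What to change.** Before each site's draw, obtain from the managers and the hospital's paging directory one list of device numbers by position and team, covering all four teams. The managers' input is still needed because the IT fields to be requested include role but not team. Write one rule for staff shared between teams, apply it to all four, and freeze the list.

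Count pages to the listed device positions, and use the number of listed positions as the denominator, in both arms. Accept later changes only from IT device-assignment records, by the same rule in both arms.

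The cost is an earlier request to the same people. Because sites are randomized one at a time, it can be adopted at every site not yet drawn. The drawback is that positions created after the freeze enter only through the IT record. The rule for shared staff makes attribution the same in both arms, but it does not change the fact that those staff work in both.

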#### Prescription drug therapy

We will examine an outcome measure originating in the evidence-based medicine paradigm. Clinical evidence-based guidelines exist [26] to support appropriate uses of drugs for treatment of diseases commonly seen in GIM patients: diabetes, community acquired pneumonia, congestive heart failure, hypertension, asthma, chronic obstructive pulmonary disorder, stroke, and acute myocardial infarction. A database exists that can be used for investigation of adherence to evidence-based prescribing practices. This database is used in the Ontario Drug Benefit (ODB) program.

For defined groups of individuals, the Ontario Ministry of Health and Long-Term Care covers most of the cost of prescription drug products listed in the ODB formulary. Importantly for our purposes, one of these groups is Ontario residents 65 years of age and older. For drug products prescribed by an authorized Ontario prescriber, the ODB program covers approximately 3,000 prescription drug products.

The ODB program pays for listed drug products for individuals eligible for ODB coverage if the drugs are purchased in an Ontario pharmacy that is on-line with the ministry's Health Network or from an Ontario doctor licensed to sell prescription drug products. In 2004–2005, 70% of ODB beneficiaries were age 65 or older. It is likely that a majority of patients admitted into and discharged from GIM wards in the participating hospital sites are in this age group. We believe that many are eligible beneficiaries under the ODB program and that a large share of their post-65 prescription drug use history will exist in databases of the ODB program.

For analyses of prescription drug therapy, subjects are patients who are admitted to GIM divisions of participating hospital sites on or after the start date of the intervention at the site, and who are discharged to home from the GIM division on or before the last day of the next full month that follows the conclusion date of the intervention period. We will construct an ODB record for these patients that extends for 60 days after their date of discharge.

